### Sample size calculation

A power calculation was conducted to determine the sample size necessary to detect changes in the primary outcome of portion size estimation (% deviance from actual). Based on proportional error reported when using an international food unit [29], detection of a 5% reduction in error was regarded as clinically important. A sample size of 84 was needed to detect a 5% reduction in portion size estimation error (from 20 to 15%) assuming an alpha of 0.05 and power of 80%. To adjust for clustering, the following correction factor was applied [1+ (m – 1) x ICC] [60], where m = students per school and ICC = the intra-class correlation coefficient (between school variance / (between school variance + within school variance). Assumptions are based on clustering at the school level (one class recruited per school, with 25 students per class), and an ICC of 0.1 based on data from a large scale study in Australian schools [61], resulting in a correction factor of 3.4. The resulting student sample is 285 students at 12 schools for a minimum detectable effect size of d = 0.62.

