### Recruitment and study participants

The CUPS trial will be conducted in primary schools from the Newcastle and Hunter region of NSW, Australia. Twelve schools from the Catholic Diocese of Newcastle-Maitland will be recruited to participate. From each school, one Stage 2 class (Year 3 and/or 4) will be invited. Students in Stage 2 will be selected as volume and capacity are introduced in this Stage in the NSW K-10 Mathematics syllabus [59]. All 44 Catholic primary schools within the Newcastle-Maitland region will be contacted to invite them into the study. If greater than twelve schools respond to participate, schools will be randomly selected. Principals, teachers, parents and students will need to provide their written informed consent. An email will be sent to the school principals containing Information Statements and Consent Forms. Principals will be followed up by either a reminder email or phone call. Upon receipt of the Principal’s consent, teachers’ Information Statements and informed Consent Forms will be provided to the school to distribute to all Year 3 and/or 4 teachers. To avoid teachers feeling pressured to participate, schools will be asked to send the information through email listings via an administrative staff member. A member of the research team will contact the teachers to organise a school visit and provide students with information about the study. All students wanting to participate in this study will be required to return a Consent Form, which has been signed by the students and their parents/guardians. Signed forms will be returned to the research team via a collection point at the school’s office. All Consent Forms collected through the school’s office will be kept confidential and individual’s privacy will remain protected.

Class groups in which the teacher has already taught all nutrition and volume capacity content covered in the planned intervention will be excluded. In addition, teachers with formal nutrition training/professional certification in nutrition or dietetics will be ineligible. All students of consenting teachers will participate in the CUPS program as part of their normal classroom activities. However, only data from students who return their consent letters will be used in analyses. Enrolment of the teachers and their students will be performed by a member of the research team. Figure 1 summarises the participant recruitment and group allocation flowchart.

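### The 80% power stated for d = 0.62 ignores that 12 schools leave only 10 between-school degrees of freedom; on the plan's own inputs power is about 73–75%

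*Protocol article*

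**What the plan says.** All of the calculation is in the protocol article under Sample size calculation. The starting point is a trial without clusters: "A sample size of 84 was needed to detect a 5% reduction in portion size estimation error (from 20 to 15" per cent), "assuming an alpha of 0.05 and power of 80" per cent. A design effect is then applied for clustering by school, assuming "one class recruited per school, with 25 students per class" and an ICC of 0.1, which gives 3.4. The conclusion is "The resulting student sample is 285 students at 12 schools for a minimum detectable effect size of d = 0.62".

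Three other sections bear on it. The abstract's Methods paragraph gives six classes per arm, and Recruitment and study participants takes one class per school and has whole schools allocated. The same section says that "only data from students who return their consent letters will be used in analyses". Statistical methods plans a linear mixed model with group, time (three visits) and their interaction, adjusted for gender and year level, with students clustered in classes.

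**The concern.** A design effect enlarges the variance of the treatment difference to reflect clustering. It does not change the reference distribution. When schools are randomised, the difference between arms is judged against variation between schools, and 12 schools in two arms supply 12 − 2 = 10 degrees of freedom for that. The two-sided 5% critical value is then 2.228, against 1.989 on the 82 degrees of freedom of a t-test on 84 individuals. The 80% was fixed at the individual stage and carried through unchanged.

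There is also little slack in numbers. Twelve classes of 25 make 300 students, so 285 is 95% of them on average, and the section states no allowance for students who do not consent or are absent.

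At stake is how a null result is read. The plan calls a 5-point reduction clinically important and implies a 20% chance of missing it. If the chance is nearer 26%, a null result would be given more weight against the intervention than the design supports.

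**Working it through.** **Inputs** (protocol article, Sample size calculation, unless noted): alpha 0.05; target power 80%; d = 0.62; raw difference 5 points; 84 students before clustering; m = 25 per class; ICC = 0.1; 285 students; 12 schools, six per arm (abstract, Methods). Sidedness is not stated. Two-sided is inferred, because a one-sided test would need only 66 (33 per arm, normal formula). The SD is not stated; d = 0.62 for 5 points implies 5/0.62 = 8.06.

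**Step 1: reproduce the plan's figure.**
- A two-sided t-test with 42 per arm (82 df) at d = 0.62 has 80.2% power; its detectable d at 80% is 0.619. So 84 and 0.62 agree.
- Design effect: 1 + (25 − 1) × 0.1 = 3.4.
- 84 × 3.4 = 285.6, stated as 285.

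**Step 2: the same inputs with school-level degrees of freedom.**
- Effective students per arm: n_eff = 6m / [1 + (m − 1) × 0.1]
- Noncentrality: ncp = 0.62 × √(n_eff / 2)
- Power: two-sided noncentral t on 10 df, critical value 2.228
- Detectable difference in points: d × 5/0.62

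| Case | Design effect | n_eff per arm | ncp | Power at d = 0.62 | Detectable d at 80% | In points |
|---|---|---|---|---|---|---|
| 300 students, m = 25 | 3.4 | 44.12 | 2.91 | 74.7% | 0.662 | 5.3 |
| 285 students, m = 23.75 | 3.275 | 43.51 | 2.89 | 74.1% | 0.667 | 5.4 |
| 285 students, stated factor | 3.4 | 41.91 | 2.84 | 72.5% | 0.679 | 5.5 |

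The second and third rows differ only in whether the design effect is recomputed for 23.75 students per school (1 + 22.75 × 0.1 = 3.275) or left at 3.4. In the third row, 82 df instead of 10 would give 80.1%, so the whole gap from 80% comes from the degrees of freedom.

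Simulated t-tests on six against six school means (400,000 runs) gave 74.6% at m = 25 and 74.4% at m = 24.

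**Step 3: fewer students per class.** The document gives no participation rate; these class sizes are assumptions.

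| Analysed per class | Share of 25 | Power at d = 0.62, 10 df | Detectable d at 80% |
|---|---|---|---|
| 20 | 80% | 72.0% | 0.68 |
| 17.5 | 70% | 70.1% | 0.70 |

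The effect is modest because at ICC 0.1 the number of schools matters more than the number of students in each.

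**Step 4: what baseline data could restore.** Suppose adjustment for baseline cuts the variance by 1 − r² at both student and school level, so that n_eff is divided by 1 − r². With 285 students (m = 23.75, 10 df), power is 78% at r = 0.3, 81% at r = 0.4 and 85% at r = 0.5. These correlations are assumed; the document states none.

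**The case against.** The strongest reply is that 74% is not the power of the planned test. Statistical methods specifies a mixed model over three visits with covariates, and schools are matched on size and socio-educational index before randomisation. The figures in step 2 are for an unadjusted, unmatched comparison of school means at follow-up. With useful baseline correlation, power could reach or pass 80%. This stands, and it limits the conclusion. A reader might infer that the trial as designed is underpowered, and the document does not support that. It supports only that the stated 80% does not follow from the stated calculation, which states no baseline correlation and claims no gain from adjustment.

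Three other strong readings should be resisted:

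- **Power is 70%.** That rests on an assumed participation rate. The document does not say whether 25 per class means enrolled or consenting students, and a loss allowance may stand in the full protocol. The 95% is an average over 12 classes, not a requirement for each.
- **The plan used a normal approximation.** It did not. The normal formula gives 41 per arm (82 in total); 84 is the t-test answer.
- **The multiplication is wrong.** It is not, and rounding 285.6 down to 285 has no consequence, since 12 classes of 25 provide 300.

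It is also fair to say that the gap is small beside the uncertainty in the ICC. On 10 df with 25 per class, an ICC of 0.05 gives 90% power and 0.15 gives 62%. That argues for showing a range, but it does not make the stated figure right at the plan's own ICC.

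**Conclusion.** The concern holds in a limited form. On the plan's own inputs (ICC 0.1, d = 0.62, two-sided alpha 0.05, six schools against six, unadjusted comparison), 285 to 300 students give about 73–75% power, not 80%. The effect detectable with 80% power is about d = 0.66–0.68 (5.3–5.5 points) rather than 0.62 (5 points). The cause is the missing allowance for 10 between-school degrees of freedom, not the design-effect arithmetic. Lower participation would cost a few points more, but the size of that loss rests on an assumed rate. Power under the planned baseline-using model is not established by the document and could lie on either side of 80%. The stated power is wrong as written and easily corrected; it does not show a failed design.

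**What to change.** Reword the conclusion of Sample size calculation along these lines: 12 schools with about 285 students give about 74% power for d = 0.62 in an unadjusted school-level comparison on 10 degrees of freedom, and the effect detectable with 80% power is about d = 0.67. Say whether 25 per class means enrolled or consenting students, and add the participation range (72% at 20 per class; 70% at 17.5 per class, with d = 0.70 detectable at 80%), labelled as an assumption.

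If the sponsor wishes to keep 80%, state power under the planned mixed model instead, with the assumed baseline–follow-up correlation and how it reduces the variance. For example, r = 0.4 gives about 81% at 285 students if variance falls by 1 − r² at both levels.

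The cost is one paragraph and, in the unadjusted version, a slightly less favourable stated power. Correcting the statement needs no extra schools and no change to allocation, outcome or analysis.

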### Intervention

The CUPS intervention will involve the implementation of an integrated teaching unit on nutrition and mathematics. Across one to four weeks, teachers will teach 4–5 lessons, each 40 min in duration, that use a nutrition context to apply learning outcomes of the NSW Mathematics K-10 syllabus [59]. Moreover, the trial will include a three-hour professional development workshop for all teachers and the provision of resources and materials for the schools to keep.

Teachers in the intervention group will be invited to attend the professional development workshop at the University of Newcastle, which will be delivered by researchers from the research team. The research team consists of professionals in the field of Education, Nutrition and Teaching. The workshop is registered and accredited with the NSW Education Standards Authority (NESA) as professional development towards maintaining teaching proficiency. The aim of the workshop is to provide the teachers with the fundamental skills to prepare, plan and implement the CUPS lessons. The workshop will include a rationale for the integration of nutrition into the curriculum, information on the Australian Guide to Healthy Eating (AGHE) [62], introduction to the teaching unit and support with implementation. The AGHE provides evidence-based recommendations about the type of foods and serve sizes individuals should eat for health and overall wellbeing [62]. Attendees will be provided with demonstrations, resources and the latest information to engage students with mathematical and nutrition concepts particularly on volume and capacity, and portion size estimation. They will be introduced to an integrated unit that involves the use of hands-on tools such as mathematics linking cubes and food models. We will discuss the relevance and need for this integrated and experiential approach to learning in primary schools. The AGHE will be used to make teachers familiar with content on healthy eating and portion size estimation. In this workshop, the majority of time will be spent on learning how to integrate the knowledge and skills into the Stage 2 Mathematics curriculum.

Following the completion of the professional development workshop, classes in the intervention group will be given a CUPS school pack containing all information and equipment needed to implement the program. The resources will include food models, mathematics cubes, a set of measuring cups, AGHE posters and brochures, plastic containers, lesson plans, presentation slides and worksheets. The CUPS lessons will specifically focus on learning appropriate portion sizes for each food group and the mathematical concept of volume and capacity. For example, students will learn how to convert volume from the number of mathematics cubes to measuring cups and vice versa. Teaching unit content will be based on the NSW K-10 syllabus and AGHE. Using learning outcomes from both Mathematics [59] and Personal Development, Health and Physical Education (PDHPE) syllabus [63] will enable students to participate in a range of integrated activities. Experienced primary school teachers and researchers in the field of Nutrition and Education developed the lessons involved in this intervention.

The lessons follow a sequence that will teach the students about nutrition concepts on portion/serve sizes in which mathematical concepts on volume and capacity are gradually embedded within each subsequent lesson. This progressive integration of mathematics concepts ensures that the students will become familiar with both subjects in a stepwise manner without being overwhelmed with new information. The first lesson introduces the students to the AGHE including food groups, number of serves per food group and examples of such serve sizes. The students will familiarise themselves with the use of mathematics cubes to estimate portion or serve sizes. In the second lesson, students move from digital examples to visual and hands-on tools such as mathematics linking cubes, measuring cups and food models to identify serve sizes. Students will be provided with the “Healthy eating for children” brochure, which includes the dietary guidelines and serve sizes for children. This lesson requires the use of this brochure for the children to compare, estimate and measure serve sizes based on their own gender and age. A third lesson will involve the comparison of nutrition labels and sugar content of multiple food items. This lesson supports the learning of what information can be found on a nutrition label and how this helps making informed decisions about the healthiness of each food item. In particular, students will identify, estimate and compare the volume of sugar expressed as cubes for the food products. The following lesson builds on the concepts learned in the second lesson in a way that it asks to compare, estimate and measure serve sizes using formal units. Instead of expressing serve or portion sizes in cubes, students will be taught how to convert cubes to cups, cubic centimetres and millilitres. The final lesson assesses students’ understanding of the nutrition and mathematics concepts by having them create a healthy lunchbox. Creating a healthy lunchbox will challenge the student to combine all knowledge and skills gained throughout the previous lessons in regards to food groups, estimating and measuring serve sizes, healthy vs unhealthy foods, and volume and capacity. Additional file 2 summarises the topics and learning outcomes covered by the lessons.

Based on their usual teaching structure, teachers in the intervention group will be asked to plan when they will use the resource material during their classes. As these teachers have to align the CUPS lessons with teaching the mathematics curriculum about “Understanding units of Measurement; volume and capacity”, they will be able to choose when to start with the teaching unit and within what time frame this will be delivered (1–4 weeks). The classroom teacher will provide the lessons to the students during regular teaching time at the primary schools. This ensures that the program will be delivered in a similar way to how it would be delivered outside of the study setting thereby increasing the likelihood of the findings representing a true effect.

Classes allocated to the usual teaching group (wait-list control) will not receive the CUPS program during the study period. Teachers in this wait-list control group will be asked to continue their usual mathematics lessons on volume and capacity. Similarly to the intervention group, teachers in this group will be asked to inform the research team of their plans for teaching volume and capacity and requested not to teach any nutrition-related content. Group comparisons will therefore provide information on the effect of the nutrition integration.

### Outcomes

A variety of both student and teacher related outcome variables will be collected to evaluate the CUPS program effectiveness. Student outcomes include measuring portion size estimation skills, nutrition knowledge, attitudes towards mathematics and their perceptions regarding the CUPS program. In addition, teachers will participate in teaching quality assessments and a semi-structured interview. All activities and assessments will be conducted in a sensitive manner by the research team and trained research assistants. All researchers will receive elaborate instructions prior to assessments to maintain consistency. Variables will be measured during several school visits at baseline, follow-up 1 (1–4 weeks post baseline visit) and follow-up 2 (4 weeks post follow-up 1). Time between data collection at baseline and follow-up visit 1 might differ between schools as teachers are able to decide when to teach the lessons across 1–4 weeks. All schools will be assessed within 1 week after concepts being taught (follow-up 1).

#### Portion size estimation skills

The primary outcome will be students’ portions size estimation skills which will be assessed by determining the ability of a student to estimate the correct portion size of a given food. Mathematics cubes will be used by the children to measure food volume of a set of food models [64]. Researchers will briefly explain the task to the children after which they are asked to perform this themselves. They will be given a variety of food models including an apple, chicken filet pieces, broccoli/cauliflower flowerets, feta cubes and penne pasta. Students will have to compare the volume of both cubes and food models to estimate the number of cubes that correspond with the portion size. The correct food volume expressed as number of cubes will be compared with student answers to determine their ability to estimate portion sizes as percentage deviance from the actual. This methodology has been used in previous research to explore individuals’ portion size estimation skills [29, 65]. Children will also be asked to report the food volume using other units of measurement (e.g. how many serves based on the AGHE). This outcome variable will be taken at all three school visits (baseline, follow-up 1 and follow-up 2).

The test will be administered under exam conditions and takes approximately 60 min to complete. Data on this outcome will be collected at all three school visits and will be analysed using overall point scores calculated from each correct answer. The survey will provide evidence of student’s knowledge for specific nutrition related topics and change over time. Alongside the nutrition knowledge survey, data on demographics (i.e., age, gender, school year, cultural background, language, and suburb) and prior nutrition knowledge will be collected via the questionnaire.

#### Attitude towards mathematics

The “How I Feel About Maths Scale” (HIFAMS) has been designed by Chapman [69]. This scale has 10 statements on different aspects of mathematics attitudes (e.g. enjoyment, value and coping). Students will rate their agreement for each statement on a five-point Likert scale ranging from strongly agree to strongly disagree (Table 1). The HIFAMS has specifically been designed for primary school children as a short test using simple language. Students will complete this scale at baseline, follow-up 1 and follow-up 2.

**Table 1 Tab1:** “How I Feel About Maths Scale” statements and scoring [69]

Statement		Score (*1 = Strongly disagree* to *5 = Strongly agree*)				
1.	Maths is boring	1	2	3	4	5
2.	Maths is too confusing	1	2	3	4	5
3.	I enjoy my maths lessons	1	2	3	4	5
4.	Maths is an important subject	1	2	3	4	5
5.	I can’t keep up with the work we do in maths	1	2	3	4	5
6.	I like maths	1	2	3	4	5
7.	I like maths more than my other school subjects	1	2	3	4	5
8.	Doing maths problems is fun	1	2	3	4	5
9.	I can’t see why I have to do maths	1	2	3	4	5
10.	Maths is a useless subject	1	2	3	4	5

#### Teaching quality

The research team will evaluate the teaching quality of multiple sessions scheduled during the program delivery. In both intervention and control groups, teaching quality related to lessons on volume and capacity will be coded using the Quality Teaching Lesson Observation Scales [70]. These scales are used to evaluate teaching behaviour divided into three dimensions: intellectual quality, quality learning environment and significance of learning. These three dimensions are further subdivided into six elements each (Table 2). Each element contains a descriptive statement which has to be rated on a scale ranging from 1 to 5. The mean of the 18 elements will be used for further statistical analysis [70]. Lessons will be observed and coded by a trained member of the study team. Training sessions will ensure that assessors have experience in this type of coding of lessons. Training includes explanation of the elements, the process of lesson observations and coding, and opportunities to practice coding of several videos which have been previously rated by experts. At least 20% of observations will be joint observation coding to determine inter-rater reliability. These joint observations involve coding discussions between assessors to attain an agreed code [71]. A random sample of participating teachers will be involved in this outcome measure. Three teachers from each study arm will be observed for four lessons which will be scheduled according to the teachers’ timeline.

**Table 2 Tab2:** Quality Teaching Model [70]

	Intellectual quality	Quality learning environment	Significance
**Elements**	Deep knowledge	Explicit quality criteria	Background knowledge
	Deep understanding	Engagement	Cultural knowledge
	Problematic knowledge	High expectations	Knowledge integration
	Higher-order thinking	Social support	Inclusivity
	Metalanguage	Students’ self-regulation	Connectedness
	Substantive communication	Student direction	Narrative

The Quality Teaching Model evaluates teaching practices and student learning divided into three dimensions: intellectual quality, quality learning environment and significance. Dimension are subdivided into six elements which each describe a statement that has to be rated on a scale ranging from 1 to 5

